### Study outcomes

The primary outcome of this trial is the 3-month change in positive and negative symptoms on the total PANSS score. Secondary outcomes are the 3-month change in the PANSS subscales, cognitive symptoms, immunological parameters (γ-interferon, IL-4, IL-6 and IL-12), and psychoactive medication taken during the trial.

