### Follow-up assessments

At one, two, and three months, and in case of withdrawal from the study, the severity of positive and negative symptoms will be reassessed using the PANSS. The cognitive tests will be repeated at three months or at study discontinuation. Blood samples will be taken at 2 and 3 months, or at withdrawal, for determination of the Aspirin levels. All assessments will be performed blind to medication status. The overview of the visits can be seen in table 1.

**Table 1 T1:** Overview of assessments/interventions

	Start of run-in	Baseline	1 Month	2 Months	3 Months (@)
Informed Consent	X	-	-	-	-
Screening	X	-	-	-	-
Pregnancy test	X	-	-	-	-
Randomization	-	X	-	-	-
Immunological parameters	X	-	-	X	X
Blood for DNA isolation	X	-	-	-	-
Aspirin concentration	-	-	-	X	X
PANSS	-	X	X	X	X
CASH (+)	X	-	-	-	-
Cognitive tests	-	X	-	-	X
Adverse events	-	-	X	X	X
Co-medication	X	X	X	X	X
Compliance	-	X	X	X	X

@ or withdrawal

+ if previous CASH is longer than 6 months ago

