### Withdrawal from the study

A patient must be withdrawn from the study when judged necessary by the responsible psychiatrist or when the patient withdraws his/her informed consent. In these instances all outcomes should be assessed.

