### Study size

The planned number of patients to be included in this trial is 80, 40 in each arm. This is sufficient to show a statistically significant difference between the intervention arms of effect size (Cohen's *d*) ≥ 0.66 for the change in total PANSS score from baseline to last follow-up. It is based on an alpha of 0.05, a power (1-beta) of 0.8 and a two-sided unpaired t-test. Further, we accounted for 10% withdrawal. It should be noted that the power of the repeated measures analyses is considerably higher.

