### Data analysis

The statistical significance of the difference in the change in total PANSS score, its subscores, cognitive functions, immunological parameters from baseline to last follow-up between the arms and psychoactive medication will be tested using a two-sided unpaired t-test and its magnitude will be supplied with a 95% confidence interval. In addition, all outcomes will be analyzed as dependent variables in repeated measurements analyses with treatment arm as the independent variable. To study whether the potentially beneficial effect of acetylsalicylic acid is modified by initial relative TH-2 reactivity, we will repeat the analyses in strata of IFN-γ/IL-4 ratio The analyses will primarily be 'intention-to-treat'. In addition, a per protocol analysis will be performed on those who showed more than 90% adherence. If despite randomization important baseline differences in prognostic factors exist, adjustments will be made by including the corresponding variables as independents in the multivariable models. Finally, the change in psychopathological symptoms will be related to the change in immunological parameters using multivariable regression models. In these analyses adjustments for confounders will be made when appropriate.

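### The primary outcome is the 3-month PANSS change, but the t-test and sample size use change to last follow-up, and the protocol conflicts on how withdrawn patients enter

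*Protocol article*

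**What the plan says.** **Outcome.** The Study outcomes section reads: "The primary outcome of this trial is the 3-month change in positive and negative symptoms on the total PANSS score".

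**Test.** The Data analysis section compares change "from baseline to last follow-up between the arms" by a two-sided unpaired t-test. Analyses are primarily intention-to-treat. A repeated-measures analysis with treatment arm as the independent variable is planned, but only as an addition.

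**Sample size.** The Study size section gives 40 patients per arm to detect a Cohen's d "≥ 0.66 for the change in total PANSS score", again measured to last follow-up. Of the calculation it says: "It is based on an alpha of 0.05, a power (1-beta) of 0.8 and a two-sided unpaired t-test". It adds that 10% withdrawal was allowed for, and that the repeated-measures analyses would have considerably more power.

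**Visits.** The Follow-up assessments section sets the PANSS schedule: "At one, two, and three months, and in case of withdrawal from the study, the severity of positive and negative symptoms will be reassessed". The month-3 column of Table 1 carries a footnote ending "or withdrawal". The section on withdrawal says: "In these instances all outcomes should be assessed". No month-3 PANSS is described for a patient who has left earlier.

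**The concern.** For a patient who completes three months, change at month 3 and change to last follow-up are the same number. For a patient who leaves early they are not. The second is then measured after a shorter and variable time on treatment.

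If such scores enter the primary t-test as endpoints, two things follow:

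- **Dilution.** Where the drug effect builds over time, early scores carry only part of it, and the estimate shrinks toward zero.
- **Bias.** Where both arms improve over time for reasons unrelated to the drug, the arm with more early withdrawals looks worse even if the drug does nothing.

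Unequal withdrawal is plausible here. The Adverse reactions section names gastrointestinal harms of the active drug, and the responsible psychiatrist may withdraw a patient when this is judged necessary, which may depend on symptoms.

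At stake is whether the headline result answers the question in Study outcomes, and whether the set of patients in the primary test is fixed before the data are seen.

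**Working it through.** **1. Reproduce the plan's figure.** Inputs from Study size: two-sided alpha 0.05, power 0.80, d = 0.66, 40 per arm, 10% withdrawal.

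- Required n per arm (normal approximation) = 2 × (1.960 + 0.842)² / 0.66² = 36.04.
- Evaluable per arm = 40 × (1 − 0.10) = 36.
- Power at 36 per arm and d = 0.66: 0.7996. The exact t-test calculation gives 0.789.
- Detectable d at 36 per arm = 2.80 × √(2/36) = 0.660.

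The stated size reproduces, so there is no arithmetic error. It reproduces with withdrawn patients counted as lost. If every patient's last score were used, 40 per arm would enter and the detectable d would be 2.80 × √(2/40) = 0.626.

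**2. Set the sections side by side.**

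| Section | What it implies for an early withdrawal |
|---|---|
| Study outcomes | No month-3 value, so no primary outcome |
| Follow-up assessments, Table 1, Withdrawal | A score is measured at withdrawal and filed with month 3 |
| Data analysis | Intention-to-treat, change to last follow-up: the patient is kept |
| Study size | 10% allowance: the patient is lost |

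**3. Dilution under the last-score reading.** Assume that the effect builds linearly over three months, that a share w withdraws equally in both arms, and that withdrawals split evenly between months 1 and 2.

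Retained share = (1 − w) + w × mean(1/3, 2/3) = (1 − w) + 0.5w.

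- w = 0.10: 0.90 + 0.05 = 0.95, so effective d = 0.66 × 0.95 = 0.627.
- w = 0.20: 0.80 + 0.10 = 0.90, so effective d = 0.66 × 0.90 = 0.594.

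Power with 40 per arm (normal approximation, SD unchanged), by the share of the month-3 effect present at withdrawal:

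| Withdrawal | None | Half | All |
|---|---|---|---|
| 10% | 0.757 | 0.801 | 0.839 |
| 20% | 0.656 | 0.757 | 0.839 |

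**4. Bias from unequal withdrawal, with no drug effect.** Assume a shared linear improvement over three months and all of the excess withdrawal at month 1. Each such patient then lacks two thirds of the improvement.

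Bias = difference in withdrawal × improvement × 2/3.

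- 10-point improvement: 0.10 × 10 × 2/3 = 0.67 PANSS points.
- 15-point improvement: 0.10 × 15 × 2/3 = 1.0 PANSS points.

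On the SD scale, take 5% versus 15% withdrawal, half of the shared improvement present at withdrawal, and a shared improvement of 0.5 to 1.0 SD. The bias is 0.10 × 0.5 × (0.5 to 1.0) = 0.025 to 0.05 SD, which is 4% to 8% of the 0.66 target. At 40 per arm, 5% versus 15% means 2 versus 6 patients.

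The documents give neither the shared improvement nor the withdrawal by arm, so steps 3 and 4 show scale only.

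**The case against.** Last follow-up can be read as the last scheduled visit. Follow-up assessments lists months one, two and three, and the Duration section puts follow-up at three months. Step 1 favours this reading, because d = 0.66 is recovered only when withdrawn patients drop out of the count. A reader might infer that the primary analysis is certainly last observation carried forward. The documents do not say so; it is an inference, though the withdrawal assessment, the Table 1 footnote and the intention-to-treat statement make it the more natural one. The month-3 reading does not rescue the text, since it leaves withdrawn patients out of an analysis described as intention-to-treat.

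A reader might also infer that the t-test treats imputed scores as observed and so understates its standard error. That does not hold. The PANSS at withdrawal is measured, and the standard error is valid for change to last assessment. The fault is that this contrast is not the month-3 effect. A month-1 or month-2 score would stand in only if the withdrawal assessment were missed.

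Finally, a repeated-measures analysis is already planned, and a separate analysis plan may settle the details of missing data. That limits the weight of the point. It does not remove a conflict that the protocol itself states about its primary endpoint.

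**Conclusion.** The point stands as an inconsistency in the primary endpoint that should be fixed. The outcome is fixed at three months, the test and power statement use last follow-up, and the withdrawal allowance fits a different analysis set from the one that the analysis text implies. On either reading, sections conflict over who enters the primary test or at what time.

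The numerical consequence is modest. At the planned 10% withdrawal about 95% of the effect is retained, and power is 0.801 against the planned 0.80 if withdrawn patients show half of the effect. A bias of 0.7 to 1.0 PANSS points needs an assumed shared improvement of 10 to 15 points and a 10-percentage-point difference in withdrawal, all at month 1. A claim that the primary result would be seriously distorted goes beyond what the documents support. The case for change rests on the mismatch and on how cheaply it can be removed.

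**What to change.** 1. Make the planned repeated-measures analysis of total PANSS at months 1, 2 and 3 the primary analysis. Include baseline PANSS and the randomisation strata (type of centre, relative TH-2 reactivity) as covariates, let the treatment effect vary by visit, and take the month-3 treatment contrast as the primary estimate.
2. State to which visit an off-schedule withdrawal PANSS is assigned.
3. Keep change to last follow-up, by t-test, as a sensitivity analysis.
4. Make Study outcomes, Study size and Data analysis name the same endpoint.

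**Cost.** No new visits or patients are needed, because monthly PANSS is already scheduled. The change is more than cosmetic, since the primary test changes and the t-test wording in Study size must be revised to match. The present calculation can stay as support: 36 per arm with month-3 data gives power of about 0.80 at d = 0.66.

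**Downside.** The model assumes that missing scores are missing at random given the observed data. That assumption should be stated, because the model does not remove bias if withdrawal depends on worsening that was never recorded.

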### Randomized intervention

Patients will be randomized in a 1:1 ratio to either supplementation of acetylsalicylic acid or placebo in addition to their current antipsychotic treatment. Randomization will be performed in strata of psychiatric center (tertiary or non-tertiary) and relative TH-2 reactivity (high/low), delineated by the median IFN-γ/IL-4 ratio. To this end a computer-generated list will be produced with allocation codes in random order, balanced in the four strata by using permuted blocks. The aspirin dose is based on a trade-off between a dose that has a relatively low risk of gastro-intestinal toxicity in young persons, and the dose that is presumed to be anti-inflammatory, the latter being adopted from therapeutic doses used in the treatment of musculo-skeletal disorder[18]. Placebo will be identically packaged, looking and tasting tablets. For optimal gastro protection, all patients (also those randomized to placebo) will be given 40 milligrams of pantoprazole daily[19].

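### The main PANSS comparison is a t-test on change that prespecifies no adjustment for baseline PANSS or the randomisation strata; it is valid, but may lose precision that costs almost nothing to recover

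*Protocol article*

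**What the plan says.** - **Endpoint** (Study outcomes): "The primary outcome of this trial is the 3-month change in positive and negative symptoms on the total PANSS score".
- **Test** (Data analysis): the difference between arms in change from baseline to last follow-up "will be tested using a two-sided unpaired t-test and its magnitude will be supplied with a 95% confidence interval". A repeated-measures analysis is added, with treatment arm as the only independent variable named.
- **Sizing** (Study size): "The planned number of patients to be included in this trial is 80, 40 in each arm". The calculation targets "effect size (Cohen's *d*) ≥ 0.66 for the change in total PANSS score from baseline to last follow-up", with two-sided alpha 0.05 and 80% power, for the same unpaired t-test, and it allows for one patient in ten withdrawing. The section adds that the repeated-measures analyses have considerably more power.
- **Randomisation** (Randomized intervention): "Randomization will be performed in strata of psychiatric center (tertiary or non-tertiary) and relative TH-2 reactivity (high/low", the latter split at the median IFN-γ/IL-4 ratio), using permuted blocks in four strata.
- **Other use of baseline data** (Data analysis): the analyses are repeated within IFN-γ/IL-4 strata to look for effect modification. Covariates are added to the models if important baseline differences appear despite randomisation. Centre type is not mentioned.

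The t-test is not labelled primary. It is so in effect, because the trial is sized on it and the other model is introduced as an addition.

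**The concern.** Baseline PANSS is measured within a week before randomisation, and both stratification factors are known by the time of randomisation. The main comparison makes limited use of this information.

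- **Baseline PANSS.** A change score gives baseline a slope of exactly 1. If the true slope of follow-up on baseline differs from 1, the residual variance is larger than it need be. A chance baseline difference between arms is then also not fully removed from the estimate.
- **Strata.** Stratified randomisation balances the arms on the strata. If the strata predict PANSS change and are left out of the model, their variance stays in the standard error although it no longer contributes to the real variability of the arm difference. The interval is then too wide and the test conservative.
- **Conditional adjustment.** Covariates enter only after imbalance has been seen. The estimate reported therefore depends on the data, and no precision is gained when the arms look balanced.

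This matters because the planned size only just meets its power target.

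**Working it through.** **Inputs from the protocol article:** 40 per arm, 10% withdrawal (36 evaluable per arm), d = 0.66 in SDs of change, two-sided alpha 0.05, unpaired t-test.

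**Assumed, not in the documents:** r, the correlation of baseline with follow-up PANSS; k = baseline SD / follow-up SD; R², the share of variance explained by the strata.

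**1. The plan's own figure.** The noncentrality is 0.66/√(2/36) = 2.80 with 70 df. Power is 0.789 by the t distribution and 0.7996 by the normal approximation, so the stated 0.8 is reproduced to within about a point. Solving for n instead gives 37 (normal) or 38 (t) per arm; divided by 0.9 this is 42 or 43 per arm, against the planned 40. There is no spare power.

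**2. Adjusting for baseline.** In units of follow-up variance, the change score has variance 1 + k² − 2rk and the ANCOVA residual has 1 − r². The variance ratio is

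VR = (1 − r²)/(1 + k² − 2rk), which is (1 + r)/2 when k = 1.

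The best slope for baseline is r/k, so fixing it at 1 costs nothing when r = k. Power follows from the noncentral t with effect 0.66/√VR and 69 df:

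| r | k = 1: VR, power | k = 0.8: VR, power | k = 0.7: VR, power |
|---|---|---|---|
| 0.4 | 0.70, 0.91 | 0.84, 0.85 | 0.90, 0.83 |
| 0.5 | 0.75, 0.89 | 0.89, 0.83 | 0.95, 0.81 |
| 0.6 | 0.80, 0.87 | 0.94, 0.81 | 0.98, 0.80 |
| 0.7 | 0.85, 0.85 | 0.98, 0.80 | 1.00, 0.79 |

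For comparison, the t-test has 0.79 throughout. With k = 1 the gain also fades at high r: power is 0.83 at r = 0.8 and 0.81 at r = 0.9. The confidence interval shrinks by the factor √VR, for example √0.75 = 0.87 at r = 0.5, k = 1 and √0.89 = 0.94 at r = 0.5, k = 0.8. A simulation of 4,000 trials of 72 patients at r = 0.5 with equal SDs gave 0.79 for the t-test and 0.885 with baseline adjustment, in line with the formula.

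A k below 1 is plausible here, because the inclusion criteria require a PANSS total of at least 60 at randomisation, which may narrow the baseline SD.

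**3. Chance imbalance.** The standard error of the baseline difference is √(2/36) = 0.24 baseline SD, so a difference of 0.25 SD is ordinary. At r = 0.5, k = 1 the SD of change equals the baseline SD (√(2(1 − 0.5)) = 1). The shift in the change-score difference is (1 − 0.5) × 0.25 = 0.125 SD of change, or 0.125/0.66 = 19% of the targeted effect.

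**4. Strata.** Simulation (40,000 runs, 72 patients, arms balanced within four strata):

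| R² | Actual type I error, t-test | Power, t-test | Power, strata in model |
|---|---|---|---|
| 5% | 0.044 | 0.79 | 0.81 |
| 10% | 0.038 | 0.80 | 0.83 |
| 20% | 0.028 | 0.81 | 0.87 |

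If the strata explain nothing, putting them in the model costs almost nothing: power is 0.788 with 67 df against 0.789 with 70 df.

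**The case against.** **The change score already uses baseline, and the t-test is valid.** Both statements are right. A reader might infer that the plan ignores baseline PANSS, or that its test is biased. The documents do not support that: baseline enters with slope 1, and the comparison is unbiased over repeated randomisations. Regression to the mean affects both arms alike in expectation and reaches the contrast only through chance imbalance. With prognostic strata omitted, the test errs on the conservative side.

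**The plan has other provisions.** It allows adjustment for observed imbalance, adds a repeated-measures analysis, and repeats the analyses by IFN-γ/IL-4 stratum. These soften the point without meeting it. The imbalance rule is triggered by the data. The repeated-measures model is supplementary and names only treatment arm. The stratum repeats address effect modification, not the precision of the overall comparison. Centre type is not used at all.

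**The gain may be small.** This stands. A reader might take the k = 1, r = 0.5 case (36/0.75 = 48, so as good as 12 more patients per arm) as the size of the loss. It is one assumed point. With a narrower baseline SD the gain can be a few points of power or none. Likewise, the documents do not show that the strata predict PANSS change; TH-2 reactivity is presented as a possible effect modifier.

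**A condensed article leaves covariates to the analysis plan.** That would answer a complaint about missing detail. Here the article names the test, bases the sample size on it, and makes covariate adjustment conditional on imbalance. The point concerns the method stated.

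**Modelling month-3 PANSS would change who is analysed.** This also stands. The plan analyses change to last follow-up and assesses patients at withdrawal, so a model restricted to month 3 would drop withdrawn patients or need a method for their missing values. The fix has to respect this.

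**Conclusion.** The concern holds as a question of efficiency and prespecification, not of validity. The main comparison fixes the baseline slope at 1, includes neither randomisation factor, and leaves other adjustment to observed imbalance. At 36 per arm and d = 0.66, adjusting for baseline raises power from 0.79 to 0.91–0.85 (r = 0.4–0.7, k = 1) or to 0.85–0.80 (k = 0.8), with no gain when r = k. Any gain from the strata depends on their being prognostic. Since r, k and R² are all assumed, the size of the loss cannot be fixed from the documents; over the values tabulated, the gain from baseline adjustment runs from nil to about 12 percentage points of power. The direction is clear and the downside of adjusting is negligible, so the change is worth recommending. Not making it would not invalidate the trial.

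**What to change.** Prespecify as the primary analysis one of the following:

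- an ANCOVA of PANSS total at last follow-up, which is the endpoint the plan already uses, so that patients assessed at withdrawal are kept; or
- the planned repeated-measures model.

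In either case include treatment, baseline PANSS total, centre type (tertiary or non-tertiary) and IFN-γ/IL-4 stratum. State which of the two is chosen, because they are not equivalent when patients withdraw. Report the adjusted difference with its 95% confidence interval. Let this replace the imbalance-triggered adjustment for these variables, and keep the unadjusted t-test as a supportive analysis.

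The cost is a change of wording and about three degrees of freedom (one each for baseline, centre type and TH-2 stratum). All covariates are already collected before randomisation, and N stays at 80.

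### Covariates enter the multivariable models only when a chance baseline imbalance is seen, and no covariate is fixed in advance, so precision is lost and the headline analysis stays open

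*Protocol article*

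**What the plan says.** All references are to the protocol article.

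- **Data analysis, test.** The between-arm difference in change "will be tested using a two-sided unpaired t-test and its magnitude will be supplied with a 95% confidence interval". Repeated-measures analyses are then added for all outcomes, with treatment arm the only independent variable named.
- **Data analysis, adjustment.** "If despite randomization important baseline differences in prognostic factors exist, adjustments will be made", by entering the variables in question into the multivariable models.
- **Study size.** The trial is sized on the unadjusted test: "It is based on an alpha of 0.05, a power (1-beta) of 0.8 and a two-sided unpaired t-test". The same section adds that the repeated-measures analyses have considerably more power.
- **Randomized intervention.** "Randomization will be performed in strata of psychiatric center (tertiary or non-tertiary) and relative TH-2 reactivity (high/low"), using permuted blocks.
- **Baseline assessments.** PANSS is scored no more than a week before randomisation.

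Baseline PANSS, centre type and TH-2 stratum are thus known for every patient at randomisation. None is named as a covariate in Data analysis.

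**The concern.** In a properly randomised trial, baseline differences are chance. A covariate sharpens the treatment comparison because it predicts outcome, and it does so whether or not the arms happen to differ on it. A rule keyed to imbalance leaves out a strong predictor that is balanced. It would also seldom select the two stratification factors, because the blocked randomisation is there to balance them.

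The rule also makes the content of the multivariable models depend on the realised allocation. That would matter little if those models were clearly secondary, but the text does not rank them against the t-test, and Study size presents the repeated-measures analysis as the more powerful one. An adjusted model whose covariates were chosen after the arms were compared could therefore be reported as the main result. At stake are some avoidable loss of precision in a trial of 80 patients and a modest freedom to choose between results.

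**Working it through.** **Inputs from the documents.** 80 patients, 40 per arm; d = 0.66 on the change in total PANSS; two-sided alpha 0.05; 80% power; 10% withdrawal, so 40 × 0.9 = 36 evaluable per arm; 1:1 allocation.

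**Assumed, with a range.** The correlation ρ of a covariate with the change score (0.2 to 0.5), the number of candidate covariates, and the threshold for an important imbalance (standardised difference above 0.25, or p < 0.05). The documents give none of these.

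**1. The plan's own figure.** n per arm = 2(1.960 + 0.842)² / 0.66² = 15.70 / 0.4356 = 36.04, and 36.04 / 0.9 = 40.04, or 80 in total. Conversely, power = Φ(0.66 × √(36/2) − 1.960) = Φ(0.840) = 0.80; the exact noncentral t calculation gives 0.789. The stated figure reproduces.

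**2. Pre-specified adjustment.** Adjustment shrinks the residual SD by √(1 − ρ²), so the effective effect size is 0.66 / √(1 − ρ²). With 36 per arm:

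| ρ | Effective d | Power |
|---|---|---|
| 0 (unadjusted) | 0.660 | 0.789 |
| 0.2 | 0.674 | 0.805 |
| 0.3 | 0.692 | 0.825 |
| 0.4 | 0.720 | 0.854 |
| 0.5 | 0.762 | 0.890 |

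For baseline PANSS itself, let r be the baseline to follow-up correlation, with equal variances assumed at the two times. The variance ratio of ANCOVA to the change score is (1 − r²) / (2(1 − r)) = (1 + r)/2. For r = 0.3, 0.5, 0.7 and 0.8 the ratio is 0.65, 0.75, 0.85 and 0.90, and power is 0.93, 0.89, 0.85 and 0.83.

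**3. How often the rule would fire.** The standard error of a standardised difference is √(2/36) = 0.236. A threshold of 0.25 is 1.06 standard errors, which chance exceeds about 29% of the time for one covariate. For three independent covariates the chance that at least one exceeds it is 1 − 0.71³ = 64%; simulation gives 83% for five. With p < 0.05 as trigger, the simulated figures are 5%, 14% and 22%.

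**4. Triggered against pre-specified adjustment** (simulation, 10,000 trials per cell, 36 per arm, power at d = 0.66):

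| Covariates | Pre-specified | Triggered, difference > 0.25 | Triggered, p < 0.05 | Unadjusted |
|---|---|---|---|---|
| One, ρ = 0.3 | 0.82 | 0.80 | 0.79 | 0.79 |
| One, ρ = 0.5 | 0.89 | 0.83 | 0.80 | 0.78–0.79 |
| Three, ρ = 0.3 each | 0.89 | 0.83 | 0.80 | 0.78–0.79 |

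**5. Type I error.** With one covariate at ρ = 0.3 to 0.5, the triggered test taken alone rejects a true null in 3.7% to 4.8% of trials. With more or stronger covariates it falls further, to about 1% in the most extreme case run (five covariates at ρ = 0.4, threshold 0.25). If a claim may rest on either the unadjusted or the triggered result, the rate is 5.0% to 6.5% over all scenarios run.

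**The case against.** The strongest reply is that the test used for sizing is fully fixed. A two-sample t-test takes no covariates, its confidence interval is specified with it, and the trigger touches only the multivariable models introduced as additional. This stands. A reader might infer that the primary p-value and interval do not come from a pre-specified procedure; the text does not support that. What remains is that no sentence says which analysis decides.

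Second, the stated power is intact. A reader might infer that the rule costs the trial some of its 80%. It does not: the triggered rule is at least as powerful as the unadjusted test, and the loss is only relative to an adjusted analysis that the protocol does not plan.

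Third, a reader might infer serious type I inflation. A simulated rate of about 7.8% can be produced, but only by including factors with no prognostic value and picking the smallest p-value. The protocol limits adjustment to prognostic factors and describes no such picking. With prognostic factors only, even smallest-p selection gave 6.6%.

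Fourth, a condensed article may leave the covariate list and the threshold to a fuller document. That is fair, and their absence is not the point. Imbalance as the trigger is stated here, and defining the threshold elsewhere would not change it.

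**Conclusion.** The point holds as a poorly chosen rule that is cheap to improve; it is not an error that undermines the trial. Adjustment in the multivariable models depends on chance imbalance, the obvious covariates are not fixed, and the deciding analysis is not named.

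At d = 0.66 with 36 per arm, and assuming a covariate correlation with the change score of 0.2 to 0.5, power is about 0.81 to 0.89 with pre-specified adjustment and 0.80 to 0.83 with adjustment triggered at a standardised difference above 0.25. The gain is about one point at the low end and six at the high end. A stricter trigger leaves power close to the unadjusted 0.79. The triggered test alone is slightly conservative. The error rate rises only if either result may be claimed, and then to at most about 6.5% in the scenarios run. All these sizes rest on assumed correlations and thresholds.

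**What to change.** Replace the imbalance rule in Data analysis with the following:

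- Name one deciding analysis of the 3-month total PANSS. It always includes baseline PANSS, centre type (tertiary or non-tertiary) and TH-2 stratum.
- Treat the other outcomes in the same way, each with its own baseline value where one is measured.
- Report the unadjusted t-test as supportive.
- Label any adjustment prompted by an observed imbalance as a sensitivity analysis.

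**Cost.** No new data are needed, since all three covariates are already collected by randomisation. The change must be made before unblinding. The deciding analysis would no longer be the t-test on which Study size rests, so that section needs a sentence saying so; the sample size stays adequate. Three covariates use three degrees of freedom out of the 70 that the t-test has with 36 per arm.
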